## Background

### Child behavioural outcomes post-TBI

Paediatric traumatic brain injury (TBI) is a leading cause of disease burden in young children [1] and is associated with a range of poor psychological outcomes [2]. This includes post-injury behaviour changes [3], which can include excessive externalising behaviour, where the child demonstrates aggression, non-compliance, and irritability [4, 5]. The child may also exhibit poor self-regulation [6] and behave inappropriately in social settings [7, 8]. Internalising behaviours may also be present, in which the child is withdrawn and anxious [3], and parents may report personality changes [9].

The prevalence of such changes have been documented in 36% of severe TBI cases and 22% of moderate TBI cases [10]. Research also suggests that young children who experience a mild TBI requiring inpatient care are more likely to have behaviour problems than their uninjured peers [11]. Indeed, Catroppa and colleagues [12] showed that behaviour problems can emerge regardless of injury severity. These changes have been demonstrated to emerge early post-injury and increase over time [10] and may persist in the long-term [10, 11]. Behaviour disturbances post-injury have the potential to set individuals on a poor long-term trajectory, which may include difficulties in the classroom [10], anti-social behaviour [4], and increased risk of criminality [13]. Thus, problematic behaviour post-TBI is an outcome which requires attention and cannot be assumed to resolve without intervention.

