## Methods/design

### Overall study design

The current pilot study employs a two-arm, parallel non-randomised design, in which a treatment as usual wait-list group is compared with a group in which the ‘Signposts’ programme is completed with clinician support via videoconferencing (see Fig. 1). The wait-list group may access any therapies or treatments considered standard treatment for a paediatric TBI.

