### Participants

Participants are the primary caregivers (herein referred to as parents) of at least one child who has sustained a TBI within the prior 2 years. Children aged 2.0–6.11 at the time of injury, who sustained mild, moderate, or severe injuries, will be eligible to participate.

Inclusion criteria for the current study are that medical records suggest that parents and children have sufficient English skills, that the child has no prior history of neurological or developmental disorder, no diagnosed severe psychiatric disorder in the parent, and no documented evidence that the TBI was non-accidental.

In keeping with previous research [38], TBI will be classified by injury severity (mild, moderate, or severe). For young children, these categories are largely based on scores on the Paediatric Glasgow Coma Scale (GCS) [39], which provides ratings of the depth and/or duration of altered consciousness post-injury. As an adaptation to the initial scale devised for use in adults [40], GCS is instead rated in young children by recording behavioural rather than verbal responses. Scores are assigned on a scale of 3–15, where 3 indicates no verbal, motor, or visual responsiveness to stimuli, and 15 indicates full responsiveness.

Classifications of injury severity are made according to the following criteria:(i)Mild: GCS 13–15, no evidence of mass lesion on CT/MRI and no neurological deficits(ii)Moderate: GCS 9–12, mass lesion or other evidence of specific injury on CT/MRI and/or neurological impairment(iii)Severe: GCS 3–8, mass lesion or other evidence of specific injury on CT/MRI and/or neurological impairment

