### Procedure

#### Recruitment

Eligible parents are identified by clinicians working in relevant departments at the Royal Children’s Hospital and the Victorian Paediatric Rehabilitation Service in Melbourne. Parents will then be allocated to either the intervention or wait-list control group on an alternating basis according to date of injury.

Recruitment letters will be mailed to parents, introducing the study and inviting them to participate. Parents are provided with information statements and sign the consent form should they wish to participate. Parents who do not accept or decline participation within 2 weeks will be followed up with a phone call.

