### Sample size

The current feasibility study sample will aim to consist of 15 parents who will participate in the intervention and a further 15 allocated to the wait-list control group. Studies also exploring the feasibility of family-centred behaviour interventions in this population used similar sample sizes [49–52] and detected promising preliminary results. With recruitment in this population frequently difficult and slow, we aim to measure the duration of time taken to recruit this sample in order to guide estimates of recruitment duration for a larger RCT.

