### Data analysis

Frequencies and percentages will be used to describe the population across key demographic and injury variables. We will compare the intervention and wait-list control groups across key variables (age at injury, injury severity, social risk, pre-injury behaviour, and pre-intervention behaviour) to detect any significant difference which may later compromise the generalisation of the findings.

Investigating the feasibility, clinical practicality, and acceptability of Signposts with videoconferencing support will be exploratory in nature. The objective is to collect information on ease of use, participant satisfaction, homework completion rates, programme completion and adherence, and attrition rates. Rates of programme attrition will be reported, as well as consumer satisfaction with the programme (reported as mean scores and percentages for items on the CSS).

To examine preliminary data on the impact of the programme on key outcome areas, we will compare the post-intervention scores on the CBCL scales, FAD, DASS, PS, and PSOC across the intervention and control groups and will report the mean and standard deviation of each group across these measures. To report preliminary findings on the maintenance of any treatment effects, means and standard deviations will be reported to assess any change within the intervention group from post-intervention to 4-month follow-up across the CBCL scales, FAD, DASS, PS, and PSOC. These findings may inform efficacy estimates for a larger RCT.

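### Allocation alternates on injury date alone, so with 15 per arm a chance imbalance in injury severity is likely enough to justify a second allocation list, although its effect on the exploratory comparison is small

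*Protocol article*

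**What the plan says.** Overall study design declares the type of study: "The current pilot study employs a two-arm, parallel non-randomised design". Recruitment gives the whole allocation rule: families go to one arm or the other "on an alternating basis according to date of injury". The next paragraph of that section turns to the invitation: "Recruitment letters will be mailed to parents, introducing the study and inviting them to participate". Allocation is therefore described before invitation and consent.

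Participants admits all three severity grades, with no quota and no expected mix, and says that "TBI will be classified by injury severity (mild, moderate, or severe"). The grades rest on the Glasgow Coma Scale, imaging and neurological signs. Intervention procedure requires at least 3 months between injury and the start of the programme.

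Sample size aims for "15 parents who will participate in the intervention and a further 15 allocated to the wait-list control group". Data analysis compares the arms on "age at injury, injury severity, social risk, pre-injury behaviour, and pre-intervention behaviour", looking for significant differences. It then reports post-intervention means and standard deviations by group, which may inform efficacy estimates for a larger trial.

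On the link to outcome, the Background reports behaviour changes in "36% of severe TBI cases and 22% of moderate TBI cases". It gives no rate for mild injury and adds that problems can arise at any severity.

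**The concern.** Alternating down a list ordered by injury date spreads time since injury evenly but leaves severity to chance. The protocol does not say in words that severity is known at allocation. It follows from the acute data used for grading and from families being identified by clinicians at the treating services. The plan thus names severity as a variable that matters, could have it in hand, and looks for an imbalance only afterwards.

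At stake is the fourth objective in Study aims, the preliminary comparison with the wait-list group. It contrasts two groups of 15, where a few children more or less in one severity class make up a sizeable fraction of an arm. This is separate from the predictability of alternation: a concealed allocation from a single list would leave severity equally to chance.

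**Working it through.** The protocol gives no imbalance figure, expected severity mix, alpha or power, so there is nothing of its own to reproduce.

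**Inputs.** From the document: 15 per arm (Sample size) and a CBCL T-score SD of 10 (Child behavioural outcomes). Assumed: injury-date order is unrelated to severity; K = 6 to 20 moderate/severe children among 30, or a share p of 20–50%; moderate/severe children score 5 T points higher (half of the stated SD); consent of 30–80%.

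**1. Imbalance with K fixed.** Let X be the number of moderate/severe children in one arm, X ~ Hypergeometric(30, K, 15), and D = |2X − K|. For K = 15, D ≥ 3 means X ≤ 6 or X ≥ 9.

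| K | P(D ≥ 3) | P(D ≥ 5) |
|---|---|---|
| 6 | 16.9% | 1.7% |
| 8 | 21.5% | 3.5% |
| 9 | 42.7% | 10.9% |
| 10 | 24.5% | 5.0% |
| 12 | 26.4% | 6.0% |
| 15 | 46.6% | 14.3% |
| 18 | 26.4% | 6.0% |
| 20 | 24.5% | 5.0% |

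An odd K allows only odd differences and an even K only even ones, so odd K gives the high values. The range is 17–47% for 3 or more and about 2–14% for 5 or more.

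**2. Imbalance with K not fixed.** The difference of two independent Binomial(15, p) counts smooths out the parity effect.

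| Share p | P(D ≥ 3) | P(D ≥ 5) |
|---|---|---|
| 20% | 24.9% | 3.8% |
| 30% | 31.8% | 7.1% |
| 40% | 35.1% | 9.2% |
| 50% | 36.2% | 9.9% |

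**3. Would the planned check flag it?** The article names no test; take Fisher's exact test at 5%. With equal arms, its two-sided p value is the tail P(D ≥ observed) from step 1. Hence 9 vs 6 gives p = 0.47, 10 vs 5 gives 0.14 and 7 vs 2 gives 0.11. With K = 15 the split must reach 11 vs 4 (p = 0.027) to be significant. A difference of 5 reaches 5% only in an extreme case such as 5 vs 0, where p = 2 × C(15,5)/C(30,5) = 6006/142506 = 0.042.

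**4. Effect on the contrast.** Shift = (D/15) × 5: for D = 3 it is 1.0 T point, and for D = 5 it is 1.67. The standard error of the difference is 10 × √(2/15) = 3.65.

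**5. Loss of precision.** At p = 40%, severity contributes 5² × 0.4 × 0.6 = 6 of the variance of 100. Balancing it would lower the standard error from 3.65 to √(94 × 2/15) = 3.54, about 3%.

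**6. Two lists.** If every allocated family enrols, or if allocation follows consent, the moderate/severe counts differ by at most 1. With allocation before consent, simulation at p = 40% (alternating until each arm has 15) gives P(D ≥ 3) as follows.

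| Consent | One list | Two lists |
|---|---|---|
| 80% | about 35% | about 6% |
| 50% | about 35% | about 20–21% |
| 30% | about 35% | about 27–28% |

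**The case against.** The strongest reply is that this is a declared non-randomised feasibility pilot, that no stated figure is wrong, and that the choice of severity over the other four listed variables is the reviewer's. Pre-intervention behaviour, which the plan also compares, would show directly whatever severity had already done to the outcome measure. These points stand as limits on weight. They do not remove the mismatch between naming severity as a key variable and leaving it to chance.

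A reader might infer several stronger things that the document does not support:

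- *That imbalance could be prevented at no cost.* Recruitment describes allocation before invitation and consent, so two lists balance families allocated, not families enrolled. At 30% consent most of the imbalance remains.
- *That a difference of 3 or more occurs in nearly half of such studies.* The 43% and 47% figures belong to odd K. Neighbouring even values give 22–26%, and no severity mix is stated.
- *That the protocol's rates justify splitting mild from moderate/severe.* The 36% and 22% compare severe with moderate, so that gradient lies inside the pooled class. No mild rate is given, and the Background says problems can arise at any severity.
- *That the comparison is biased by confounding.* If date order is unrelated to severity, the imbalance has mean zero over repetitions and is already part of sampling error.

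**Conclusion.** The point holds as a cheap improvement in design, not as a flaw in the study's main purpose. Differences of 3 or more moderate/severe children are common (17–47% over the range of K, 25–36% for a 20–50% share). Differences of 5 or more are uncommon (about 2–14%). A significance check would seldom reveal either.

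The effect is a small loss of precision in an exploratory comparison: a shift of 1.0–1.7 T points when such an imbalance occurs, under half of the standard error of about 3.7. The primary aim of feasibility and acceptability is untouched.

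The probabilities rest on an assumed severity mix and on date order being unrelated to severity. The size of the shift rests on an assumed 5-point difference for which the document gives no source; if severity has little bearing on behaviour here, the gain shrinks accordingly.

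**What to change.** Keep two date-ordered lists, mild and moderate/severe, and allocate within each. Preferably allocate after consent, so that the enrolled counts differ by at most 1 per list. If allocation must stay before consent, use the lists all the same and state that they reduce imbalance among enrolled families without removing it.

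In Data analysis, show the severity distribution by arm descriptively and do not rely on a significance test to judge comparability.

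The cost is one more list, with no extra families or visits. Each list may end on an odd number, so arm sizes may differ by one or two. Two alternating lists remain as predictable as one; that weakness needs its own remedy.

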#### Data collection

Data will be recorded to capture the number of eligible parents approached, the number who consented to the programme, and the number who successfully completed the programme, as well as reasons for non-participation and non-completion.

Questionnaires will be administered using a secure online data collection instrument (RedCap), with parents sent web links at the appropriate time points. Upon enrolment in the study, parents will be sent the web-link questionnaires and asked to complete the outcome measure questionnaires retrospectively, reporting on their child and family’s functioning prior to the TBI. It is acknowledged that this may be vulnerable to parent reporting bias, particularly where children are several years post-injury. However, evidence suggests that post-TBI behavioural problems may not emerge or present for intervention until several years post-injury [10, 11], which means that including families several years post-injury more closely mirrors the clinical setting. It therefore seems reasonable to include such families in this feasibility study. Future research may aim to minimise this bias by reducing the eligible time since injury.

Prior to commencing the programme, approximately 1 month following initial questionnaire completion, parents will be asked to complete the measures again with regard to their family and child’s *current* functioning. Outcome questionnaires will again be sent in the form of web links via email immediately after the intervention and 4 months post-intervention. The approximate timeline for completion of these questionnaires is summarised in Table 2.

**Table 2 Tab2:** Summary of measures used

Construct	Measure	Time point			
		1	2	3	4
Socioeconomic status	Social Risk Index	●			
Outcome measures					
Child behavioural outcomes	Child Behavior Checklist	●	●	●	●
Family outcomes	McMaster Family Assessment Device	●	●	●	●
Parental functioning					
Parental psychological distress	Depression Anxiety Stress Scales	●	●	●	●
Confidence and satisfaction in the parenting role	Parenting Sense of Competence Scale	●	●	●	●
Disciplinary practices	Parenting Scale	●	●	●	●
Programme satisfaction	Consumer Satisfaction Scale			●^a^	

Time point 1 = retrospectively completed about pre-injury behaviour, 2 = pre-intervention, 3 = post-intervention, 4 = 4 months post-intervention

^a^Intervention group only

#### Intervention procedure

Prior to commencement of this study, the Signposts clinician will complete the Professional Training Workshop through the Parenting Research Centre in Melbourne, where the original Signposts programme was developed. Workbooks and modules used in the current study are in the original hard copy form, available through the Parenting Research Centre. In addition, this project uses the stand-alone adjunct module ‘Dealing with a head injury in the family’, developed by Woods and colleagues [20].

Children must be at least 3 months post-injury before their parents commence the programme. When ready to commence the programme, participants engage in an initial face-to-face interview with the Signposts clinician, which provides the opportunity to build rapport and further explain the requirements of the programme, including demonstration of the iPads and the videoconferencing software. Initial modules required to begin the programme (1–3, 8, and 9) are provided at this session. The programme is commenced after this initial interview.

Parents work through module booklets in their own time and complete the relevant tasks in their workbook. On five occasions, approximately 2 weeks apart, parents engage in a one-on-one videoconference session with the Signposts clinician. The session follows the suggested structure for telephone support from the practitioner manual, which generally aims to support parents in completing homework and answer any questions or concerns that may arise.

In line with previous research [21], some programme modules were grouped together for logistical purposes. The approximate timeline for the completion of modules and videoconference sessions is presented in Table 3. Aside from the initial modules provided at the pre-intervention interview, subsequent modules (4–7) are individually sent to the family via post, as needed.

**Table 3 Tab3:** Programme for completion of Signposts programme with online clinician support

Week	Parent homework	Clinician contact
0		Pre-intervention interview
1	Read modules 1–3, 8, and 9 Begin homework	
2	Complete homework for modules 1–3, 8, and 9 prior to videoconference	Videoconference #1 Homework reviewed for modules 1–3, 8, and 9
3	Read module 4 Begin homework	
4	Complete homework for module 4 prior to videoconference	Videoconference #2 Homework reviewed for module 4
5	Read module 5 Begin homework	
6	Complete homework for module 5 prior to videoconference	Videoconference #3 Homework reviewed for module 5
7	Read module 6 Begin homework	
8	Complete homework for module 6 prior to videoconference	Videoconference #4 Homework reviewed for module 6
9	Read module 7 Begin homework	
10	Complete homework for module 7 prior to videoconference	Videoconference #5 Homework reviewed for module 7
11	Complete post-intervention questionnaires Return iPad	

### Sample size

The current feasibility study sample will aim to consist of 15 parents who will participate in the intervention and a further 15 allocated to the wait-list control group. Studies also exploring the feasibility of family-centred behaviour interventions in this population used similar sample sizes [49–52] and detected promising preliminary results. With recruitment in this population frequently difficult and slow, we aim to measure the duration of time taken to recruit this sample in order to guide estimates of recruitment duration for a larger RCT.

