### Study aims

The primary aim of the current study is to investigate the feasibility and acceptability of conducting Signposts with videoconferencing as the mode of clinician support. In particular, this study intends to investigate this in families where the child sustained the TBI in early childhood, an age group that may be particularly prone to post-TBI poor outcomes [35–37] but, to date, has been relatively neglected with minimal attention directed to development of age-appropriate evidence-based interventions targeting behaviour problems.

More specifically, the study objectives are to:Investigate the feasibility of delivering the programme with clinician support via videoconferencing, with the goal of developing a larger RCT. This will be investigated with the collection of data on sample retention rates, participant programme adherence, and duration to reach target sample size.Collect information to inform on the clinical practicality of delivery through this medium, including the duration of videoconference sessions, rate of technology difficulties that cause disruption to sessions, and the time frame for programme completion (in weeks).Explore the acceptability of the programme when delivered through this medium, with completion of a consumer satisfaction survey, as well as by enquiring on the participant’s comfort with using the technology. It is expected that, consistent with programme delivery through different modalities, the programme will have a high level of consumer satisfaction in this population when delivered with clinician support via videoconferencing.Explore preliminary clinical outcomes across those who completed the programme compared with those on a wait-list, in order to inform likely efficacy estimates for a fully powered RCT. Primary measures will assess child behaviour, while secondary outcome measures will assess parent distress, parenting disciplinary style, parenting sense of competency, and family functioning. These will be measured using questionnaires considered standard for research involving the Signposts programme (see, for example, Woods and colleagues [23]). It is expected that those who complete Signposts will report reductions in post-TBI child behaviour problems, parental distress, and dysfunctional parenting, while increasing family functioning and parental sense of competency.

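### Elapsed time to 30 families is the stated guide to RCT recruitment duration, but with a 2-year look-back it may mix a one-off backlog with new-case inflow and can then overstate the sustainable rate

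*Protocol article*

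**What the plan says.** Study aims (Protocol article) ties the first objective to developing a larger RCT and names its measures as "sample retention rates, participant programme adherence, and duration to reach target sample size". The Sample size section sets the target at "15 parents who will participate in the intervention and a further 15 allocated to the wait-list control group", remarks that recruitment in this population tends to be hard and slow, and states the aim to "measure the duration of time taken to recruit this sample in order to guide estimates of recruitment duration for a larger RCT".

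Under Participants, those eligible are primary caregivers of "at least one child who has sustained a TBI within the prior 2 years". Data collection defends the long look-back on the ground that "including families several years post-injury more closely mirrors the clinical setting". It also says, in connection with recall bias, "Future research may aim to minimise this bias by reducing the eligible time since injury". Intervention procedure adds: "Children must be at least 3 months post-injury before their parents commence the programme".

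Under Recruitment, clinicians at two services identify eligible parents. These are allocated alternately by date of injury and then sent a letter. Data collection records how many eligible parents were approached, how many consented and how many completed, with reasons for non-participation. The article does not say whether past cases are searched at opening or families are found as they present. It does not say how the measured duration will be turned into an RCT estimate.

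**The concern.** A family whose child was injured before opening can be recruited once. When those families have been approached, recruitment depends on new injuries. A single elapsed time to 30 does not show how much came from each source, and a planner given only that time cannot recover the inflow rate.

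Recruitment time is one of three named measures under the feasibility objective, and the protocol itself expects recruitment to be difficult. If the duration is read as a rate and carried to a longer trial at the same services, or to one with a shorter window, the RCT could be planned on a timeline that new cases cannot support.

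**Working it through.** **The plan's own figure.** 15 + 15 = 30 families. There is nothing further to reproduce: the target rests on similarity to earlier feasibility studies, and no recruitment rate is given.

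**Is a backlog likely to be used?** The text does not say so. Three places point that way.

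- The eligibility window (Participants) admits injuries up to 24 months old on opening day.
- Data collection treats families long after injury as wanted, not merely tolerated. (Its reference to several years sits awkwardly with the 2-year limit in Participants, and the two should be reconciled. I read it here as the upper end of the window.)
- The 3-month minimum before programme start means that any intervention family starting within 3 months of opening must come from an injury before opening. This concerns programme start, not enrolment, so it supports the inference without proving it.

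**Model and inputs.**

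- r = new consenting families per month (assumed).
- W = months of accumulated cases at opening: 24 from Participants, or 21 if the 3-month minimum is also applied at entry (24 − 3).
- q = uptake among backlog cases relative to new cases (assumed, 0 to 1).
- T = months to reach 30 (assumed, 6 to 36).
- The whole backlog is assumed to have been approached by time T.

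The 30 families are backlog plus inflow: 30 = rWq + rT, so r = 30/(Wq + T). The apparent rate is 30/T. Hence

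apparent rate / sustained rate = (30/T) / r = 1 + Wq/T.

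**Results for W = 24.**

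| T (months) | q = 1 | q = 0.5 | q = 0.25 | q = 0 |
|---|---|---|---|---|
| 6 | 5.0 | 3.0 | 2.0 | 1.0 |
| 12 | 3.0 | 2.0 | 1.5 | 1.0 |
| 24 | 2.0 | 1.5 | 1.25 | 1.0 |
| 36 | 1.67 | 1.33 | 1.17 | 1.0 |

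Top left: 1 + 24 × 1/6 = 5. Bottom of the q = 0.25 column: 1 + 24 × 0.25/36 = 1.17. With W = 21 the same two corners are 1 + 21/6 = 4.5 and 1 + 21 × 0.25/36 = 1.15.

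**What it means for an RCT of size N.** Suppose the RCT has k times the pilot's catchment and the same window, with a fresh backlog everywhere. Its recruitment time is N/(kr) − 24q.

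- Sites added in proportion (k = N/30): N/(kr) − 24q = 30/r − 24q = T. The pilot duration transfers unchanged, and nothing is overstated.
- Same services (k = 1), for illustration with assumed N = 200, r = 1, q = 1. The pilot takes T = 30 − 24 = 6 months, an apparent 5 per month. Reading that as a rate gives 200/5 = 40 months. The model gives 200 − 24 = 176 months with a fresh 2-year backlog, or 200 months from new cases only.
- Between the two (k = 4, same assumptions): 200/(4 × 5) = 10 months from the apparent rate, against 200/4 − 24 = 26 months.

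These RCT figures illustrate direction and the dependence on k. They are not estimates.

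**The case against.** The strongest reply is that the backlog is inferred. Participants gives an eligibility window, and Recruitment says only that clinicians identify parents. If cases are found as they present and none from before opening is approached, q = 0 and there is no distortion. This stands as a limit on the claim. It does not remove it, because the window, the defence of late cases and the 3-month minimum all suggest that earlier injuries will be recruited.

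Second, the protocol says the duration will guide estimates. It does not say that it will be scaled linearly. A reader might infer that the protocol commits to such a projection, or that the pilot certainly overstates the RCT rate, perhaps fivefold. The documents support neither. The fivefold case needs 30 families in 6 months and equal uptake from old and new injuries, whereas the protocol expects slow recruitment. Slow recruitment is where the ratio is smallest: 1.17 to 1.67 at 36 months for q from 0.25 to 1.

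Third, the RCT's design is open. Videoconferencing is meant to reduce geographical barriers, so a wider catchment is plausible, and with sites added in proportion and the same window the problem vanishes. The remark about a shorter window is tentative and concerns recall bias. Both points are right, and they make the conclusion conditional.

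Fourth, the counts needed for a better projection are already collected, and a journal article need not spell out reporting detail. The first half is true and makes the remedy cheap. The second does not dispose of the point, because the article does not leave the planning quantity open: it names elapsed time.

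**Conclusion.** The point holds in conditional form. If families injured before opening are approached, elapsed time to 30 mixes a one-off stock with inflow. It can then overstate the sustainable rate for an RCT that stays longer at the same services or uses a shorter window. It does not do so for one that adds sites in proportion with the same window.

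The factor is 1 + 24q/T: about 1.2 to 5 over T = 6 to 36 months and q = 0.25 to 1, and 1.0 if no backlog is used. It rests on assumed values of q and T, a constant inflow and a backlog fully approached by time T. No incidence, consent rate or duration in the documents narrows it. The plan contains no wrong figure here. The weakness lies in the quantity chosen to inform the RCT, and it is worth correcting because a better one is available from data the study will hold.

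**What to change.** In Study aims, Sample size and Data analysis, keep elapsed time to the target as a description and name different quantities as the guide for the RCT:

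1. Numbers eligible, approached and consenting, reported separately for children injured before and after recruitment opened.
2. The monthly inflow of eligible families, by calendar month of injury.
3. An RCT projection equal to inflow times consent fraction, plus a one-off backlog term calculated for the RCT's own window and sites.

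The article should also state whether past cases are searched at opening.

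Little new data collection is needed. Date of injury is known because allocation uses it, and numbers approached and consenting are recorded. If some identified families are never approached, a count of those identified must also be kept.

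The costs are slightly more reporting, a less favourable projection, and imprecision where few cases arise after opening. For example, 6 new-case families give a relative standard error of about 1/√6 = 41% under a Poisson assumption, so the inflow should be given with an interval.
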